| Demographic and sociodemographic  surveys, obstetrics and gynecology^3)^ | | ● |  |  |  |  |
| Investigate medical and medication  history^4)^ and identify changes | | ● | ● | ○ | ● | ● |
| Constitutional Diagnosis Questionnaire  (KS-15) | | ● |  |  |  |  |
| Inspect | |  |  |  |  |  |
|  | General physical exam | ● | ● | ○ | ● | ● |
|  | Thermometer measurement^5)^ | ● | ● | ○ | ● | ● |
|  | VAS of coldhypersensitivity in the hands and feet | ● | ● | ○^6)^ | ● | ● |
|  | Screening for and identifying  adverse events |  |  | ○ | ● | ● |
|  | Pattern Identification Questionnaire | ● |  |  |  |  |
|  | Coldness Diagnostic Questionnaire |  | ● |  | ● | ● |
|  | Quality of Life Assessment  Questionnaire (WHOQOL-BREF) |  | ● |  | ● | ● |
|  | Quality of Life Assessment EQ-5D |  | ● |  | ● | ● |
| Laboratory tests | | ●^7)^ |  |  | ○ |  |
| Acupuncture or electroacupuncture | |  | ○ | ○ | ○ |  |
| Specify next visit date | |  | ● | ○ | ● |  |
| Examiner signature | | ● | ● | ● | ● | ● |

● Conduct all three groups

○ Acupuncture treatment group, pre-acupuncture treatment group only

■ No-treatment control visit date

1. Screening includes chest x-ray and electrocardiogram
2. Performed at screening
3. Age, occupation, digestion, exercise, smoking, drinking, sleep, and motivation t o participate
4. Include a medical and medication history related to coldhypersensitivity in the hands and feeet
5. Temperature measured at bilateral anterior thigh (ST32) and dorsum of the foot (LR3) and the palm (PC8) and arm (LU4) sites at each visit
6. The acupuncture group and the electroacupucnture treatment group additionally measured the hands and cold coldness VAS at visit 4 and visit 8.
7. Screening includes hematologic tests (WBC, RBC, Hemoglobin, platelet), blood chemistry tests (BUN, creatinine, AST, ALT, r-GTP, glucose), thyroid function tests (free T4, TSH), urine and urinalysis, and pregnancy test (Urine HCG). At D35 (Visit 10), hematology (WBC, RBC, Hg, platelet), blood
[figure not shown]
 chemistry (BUN, creatinine, AST, ALT, r-GTP, glucose) will be performed.

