##### Secondary purpose

##### The efficacy of the study will be further evaluated by comparing the changes in scores on the Visual Analog Scale of coldhypersensitivity in the hands and feet, body temperature (thermometer measurement), Quality of Life Assessment Questionnaire (WHOQOL-BREF), Quality of Life Assessment EQ-5D, pattern identification questionnaire, and coldness diagnostic questionnaire between the no-treatment control group, acupuncture treatment group, and electro-acupuncture treatment group.

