Sensory, musculoskeletal, endocrine, multiple, urinary, reproductive, digestive, cardiovascular, nervous, dermatologic, and estrogenic systems. Obtain a history of renal, hematologic, lymphologic, respiratory, and other medical and medication history. Any significant findings o n examination at the initial visit should be recorded in the other organ systems section of the case record sheet, and any significant medical findings that meet the definition of an adverse event after initiation of the study procedure should be recorded on the adverse event sheet.

- - - 1. Visual Analog Scale (VAS)

Assess at each visit. At each visit, a VAS for the degree of coldhypersensitivity in the hands and feet will be completed by the participants with the assistance of the investigator.

- - - 1. Pattern Identification Questionnaire and Constitutional Diagnostic Questionnaire (KS- 15)

Administered at Visit 0.

Two principal investigators or a Korean medicine doctor will evaluate the participants.

The evaluator checks the items and marks ◯ on the most appropriate item to indicate the degree of the condition the participant has through the pattern.

The evaluator marks the corresponding pattern identification with a ◯.

- - - 1. Vital signs and height and weight measurements

Vital signs are assessed at every visit. Vital signs include blood pressure, pulse rate, and temperature. Height is measured only at Visit 0, and weight is measured at Visits 0, 10, and 11.

- - - 1. Determining conformance to inclusion/exclusion criteria

At Visit 0, consent, demographic and sociodemographic information, medical and medication history, laboratory tests, pregnancy test and chest x - ray, electrocardiogram, and thermometer measurements to determine if the participant meets the cold diagnostic criteria will be taken.

- - - 1. Check for changes in medical and treatment history

Inquire at each visit whether there have been any changes in medical and treatment history since Visit 0 (Screening). Inquire about any changes compared to what was identified in the drug history screening at Visit 0. If there are any changes in concomitant medications, document them in detail in the case record.

- - - 1. Clinical examination items

Obtain written informed consent and perform a 12-lead EKG, chest x-ray, and examination of the following on Visit 0

①Hematological tests: WBC, RBC, Hemoglobin, Platelet

②Blood biochemical tests: BUN, Creatinine, AST, ALT, r-GTP, Glucose

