**Clinical trial flowchart**

| Recruitment and Informed Consent (Visit 0) |
| --- |

↓

| Screening |
| --- |
| Vital signs, height, weight, pathways to and motivation for study participation, demographic and sociodemographic surveys, obstetrical Informational history, medical history and medication history, general physical examination, thermometer measurement, VAS of coldhypersensitivity in the hands and feet, pattern identification questionnaire, laboratory test, Chest X-ray, ECG, Determination of exclusion criteria |

↓

| Randomization |
| --- |
| Acupucnture treatment group, Electroacupuncture treatment group, Control group |

↓

| Baseline (0week) Evaluation (Visit 1) |
| --- |
| Vital signs, weight, medical history and medication history and changes, constitutional diagnostics questionnaire (KS-15), general physical examination, thermometer measurement, VAS of coldhypersensitivity in the hands and feet, quality of life assessment questionnaire (WHOQOL-BREF), quality of life assessment EQ-5D, coldness diagnostic questionnaire, treatment, scheduling next visit |

↓

| Acupuncture or Electroacupuncture treatment (Visit 2~9) |
| --- |
| Acupuncture or electroacupuncture treatment for 5 weeks, vital signs, medical history and medication history and changes, general physical examination, thermometer measurement, VAS of coldhypersensitivity in the hands and feet, checking for adverse events, laboratory tests, scheduling next visit |

| Week 5 Evaluation (Visit 10) |
| --- |
| Vital signs, weight, medical history and medication history and changes, general physical examination, thermometer measurement, VAS of coldhypersensitivity in the hands and feet, quality of life assessment questionnaire (WHOQOL-BREF), quality of life assessment EQ-5D, coldness diagnostic questionnaire, checking for adverse events, laboratory tests, scheduling next visit |

↓

| Daily routine for 4 weeks |
| --- |

↓

| Week 9 Evaluation (Visit 11) |
| --- |
| Vital signs, weight, medical history and medication history and changes, general physical examination, thermometer measurement, VAS of coldhypersensitivity in the hands and feet, quality of life assessment questionnaire (WHOQOL-BREF), quality of life assessment EQ-5D, coldness diagnostic questionnaire, checking for adverse events |

↓

| Data cleaning and statistical processing |
| --- |

↓

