#### Observation and inspection items

|  | | Screening | Treatment period | | | |
| --- | --- | --- | --- | --- | --- | --- |
| Visit | | (D -7~0) | Visit 1  (D 1) | Visits 2-9 | Visits 10  (D 35±3) | Visit11  (D 63±3) |
| Obtain written consent | | ● |  |  |  |  |
| Assign a screening number | | ● |  |  |  |  |
| Chest X-ray & EKG^8)^ | | ● |  |  |  |  |
| Inclusion/exclusion criteria^9)^ | | ● |  |  |  |  |
| Randomization | |  | ● |  |  |  |
| No-treatment control group | |  | ■ |  | ■ | ■ |
| Assess treatment adherence | |  |  | ○ | ○ | ○ |
| Whether participants drop out of the study | |  |  | ○ | ○ | ○ |
| Vital signs | | ● | ● | ○ | ● | ● |
| Height, weight, and body mass index (BMI) | | ● |  |  | ●  (Weight only) | ●  (Weight only) |
| Pathways and motivations to participate in  research | | ● |  |  |  |  |
| Demographic, sociodemographic, gynecologic and obstetric information^10)^ | | ● |  |  |  |  |
| Investigate medical and medication  history^11)^ and identify changes | | ● | ● | ○ | ● | ● |
| Constitutional Diagnosis Questionnaire (KS-15) | | ● |  |  |  |  |
| Inspection | |  |  |  |  |  |
|  | General physical exam | ● | ● | ○ | ● | ● |
|  | Thermometer measurement^12)^ | ● | ● | ○ | ● | ● |
|  | VAS of coldhypersensitivity in the hands and feet | ● | ● | ○^13)^ | ● | ● |
|  | Screening for and identifying  adverse events |  |  | ○ | ● | ● |
|  | Pattern identification questionnaire | ● |  |  |  | ● |
|  | Coldness diagnostic questionnaire |  | ● |  | ● | ● |
|  | Quality of life assessment  questionnaire (WHOQOL-BREF) |  | ● |  | ● | ● |
|  | Quality of life assessment EQ-5D |  | ● |  | ● | ● |
| Laboratory test | | ●^14)^ |  |  | ○ |  |
| Acupuncture or electroacupuncture treatment | |  | ○ | ○ | ○ |  |
| Specify next visit date | |  | ● | ○ | ● |  |
| Examiner signature | | ● | ● | ● | ● | ● |

● Conduct all three groups

○ Acupuncture treatment group, electroacupuncture treatment group

■ No-treatment control group

1. Chest x-ray and electrocardiogram performed during screening
2. Performed at screening
3. Age, occupation, digestion, exercise, smoking, drinking, sleep, and motivation to participate
4. Include a medical and medication history related to coldhypersensitivity
5. Bilateral temperature measurements of the anterior thigh (ST32), dorsum of the foot (LR3), palm (PC8) and arm (LU4) at each visit

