In a room at 24±2°C, and 40-60% humidity, expose at least 10cm above both elbows, sit and rest for 10 minutes with lower extremity clothing up to the knee, and take three consecutive measures using a non-contact infrared thermometer at a distance of approximately 3cm from the anterior thigh (ST32), dorsum of the foot (LR3), palm (PC8), and arm (LU4), and record the median value, excluding the highest and lowest values.

- - 1. Hands and Feet Coldness (Visual Analog Scale: VAS)

The VAS of coldhypersensitivity in the hands and feet will be completed by the participants with the assistance of the researcher. On the VAS, participants will mark an “I” for their level of hands and feet coldness.

O, V, not verbalized (to be precise)

[figure not shown]

[figure not shown]
Using a horizontal straight line labeled with numbers from 0 to 10 before the start of the acupuncture treatment and after the end of the treatment, have the participants select the number that corresponds to their level of fatigue. At the left end of the straight line, add the description 'no cold' and at the right end, 'the most severe cold imaginable'. The score is the number they choose.

Only those who have a temperature difference of 0.3℃ or more between the palm (PC8) and arm (LU4) or a temperature difference of 2℃ or more between the anterior thigh (ST32) and dorsum of foot (LR3) measured by a thermometer at the time of the screening visit and a Visual Analogue Scale (VAS) of coldhyepersensitivity in the hands or feet of 4 or more will be enrolled.

- - 1. Pattern identification questionnaire

At Visit 0, the principal investigator or research associate will evaluate participants.

1. The evaluator checks the most appropriate condition for the participants and ◯ marks.
2. The evaluator marks the corresponding pattern identification with a ◯.
   - 1. Constitutional Assessment Questionnaire (KS-15)

Conducted by the principal investigator or research associate at Visit 0

- - 1. Laboratory tests

At visit 0, a 12-lead EKG, chest x-ray, and the following tests are performed

① Hematologic tests: WBC, RBC, Hemoglobin, Platelet;

② Blood biochemistry test: BUN, creatinine, AST, ALT, r-GTP, glucose

③ Urine and urine specimen tests: Blood, Urobilinogen, Bilirubin, Ketone, Protein, Nitrate, Glucose, pH, S.G, LEU, WBC, RBC

④ Pregnancy test (women of childbearing age): Urine HCG;

⑤ Thyroid function tests: free T4, TSH

- - 1. Determining conformance to inclusion/exclusion criteria

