##### Score:

- 1. **Secondary outcome variable**
     1. Body temperature: Thermometer measurement
- The difference in temperature between the bilateral palm (PC8), arm (LU4), anterior thigh (ST32), and dorsum of foot (LR3) regions, measured within 10 minutes of each visit, before the start of treatment and after the end of treatment, respectively, using a thermometer

[figure not shown]

[figure not shown]

[References]

Lee MJ, et al. A clinical case study to evaluate the hot flush and abdominal cold hypersensitivity relief efficacy of Cheonglijagamtang in climacteric women by DITI. Journal of oriental medical thermology. 2010;8(1):26-32.

Kim EG, et al. A clinical case study for the diagnosis and assessment of abdominal cold hypersensitivity treatment by DITI. Journal of oriental medical thermology. 2009:7(1):55-65.

Cho JY, et al. A case report of cold hypersensitivity of hands and feet patient. The journal of oriental obstetrics & gynecology. 2011;24(3):195-202.

Lee YJ, et al. Effects of far-infrared rediating products on coldhypersensitivity of lower limbs using cold stress test (CST): a pilot study. Journal of oriental medical thermology. 2008;6(1):69-75.

- - 1. Quality of Life Assessment Questionnaire (WHOQOL-BREF) and Quality of Life Assessment EQ-5D
- Overall quality of life, general health, physical health, psychological health, social relationships, and environment, measured at visits 1, 10, and 11.
  - 1. Pattern Identification Questionnaire
- Pattern identification questionnaire measured at visit 1 to correlate symptoms and VAS changes in patients with cold feet according to dialectic indicators.
  - 1. Coldness Diagnostic Questionnaire
- Coldness Diagnostic Questionnaire, which asks participants about their subjective or objective symptoms of coldness, is measured at Visit 1, Visit 10, and Visit 11.

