a. Construct validity: The construct validity is evaluated by conducting a factor analysis of the items of the basic dialectic tool. After obtaining the scores of each item of the basic argumentation tool, the correlation matrix between the items is obtained. Determine the number of factors by the eigen value of the factor, rotate the factor after checking the construct validity, and interpret and name the items with large factor loadings related to the rotated factor based on the content of the items. b. Predictive validity: Evaluate the correlation between the values of the visual analog scale and the scores of the factors explaining cold feet. It estimates the degree of correlation between the visual analogue scale values of participants with coldhypersensitivity in the hands and feet and the sum of the scores of items that can well explain coldhypersensitivity in the hands and feet. Cronbach's alpha was measured to evaluate the questionnaire. In addition, we will analyze the changes i n the items and the magnitude of each item before and after the treatment, and the magnitude of the treatment effect for each specific type of excuse. In addition, we will use cluster analysis or factor analysis to identify the association and excuse relevance of excuse items related to coldhypersensitivity in the hands and feet.

- - - 1. Coldness Diagnostic Questionnaire:
         - Cronbach's alpha is used to analyze reliability. We also use the statistical method of Item-Total Correlation to analyze the correlation between items by measuring the Pearson correlation coefficient between the total scores of the remaining items.
         - Perform additional cluster analysis and factor analysis.
      2. Quality of life assessment EQ-5D: The EQ-5D index score does not have an officially established cutoff value to assess impaired health-related quality of life, but it is utilized for economic evaluation using the 4th and 5th quintiles.

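### The pattern identification questionnaire has three conflicting schedules, none with a Visit 10 measurement, yet its pre/post and between-arm change are to be analysed

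*Protocol*

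**What the plan says.** **Timing.** The protocol gives three versions.

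- *Screening only.* The Summary of Clinical Study Schedule has a row for the "Pattern Identification Questionnaire" marked in the screening column alone. The Trial Schedule text says "Administered at Visit 0". The flowchart puts it in the screening box and no other ("pattern identification questionnaire, laboratory test, Chest X-ray, ECG"). The Visit 0 procedures agree: "At Visit 0, the principal investigator or research associate will evaluate participants".
- *Screening and Visit 11.* The table under Observation and inspection items has the row "Pattern identification questionnaire" marked for all three groups at screening and again at Visit 11.
- *Visit 1.* The secondary outcome section reads "Pattern identification questionnaire measured at visit 1 to correlate symptoms and VAS changes".

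**Analysis.** The Secondary purpose evaluates efficacy through changes in a list of scores that ends "pattern identification questionnaire, and coldness diagnostic questionnaire between the no-treatment control group, acupuncture treatment group, and electro-acupuncture treatment group". The section on analysing validity variables covers changes in the items and "the magnitude of each item before and after the treatment", and the Statistical analysis row of the overview carries the same commitment. The general principles under Statistical Methods define the basic efficacy analysis as the change from the baseline test to the test at the end of the trial.

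**The concern.** A change score needs one value before treatment and one after it. Most of the places that time this questionnaire provide only the first, while three places plan an analysis that needs both.

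The three sites could follow different parts of the document and collect different data. A visit at which the instrument was not completed cannot be recovered later, and no statistical analysis plan can supply it. At stake are the pre/post analysis of pattern items and the three-arm comparison of change in this questionnaire. It is a listed secondary outcome, so the damage does not reach the primary endpoint.

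**Working it through.** No sample-size, power or alpha figure enters this point. The check sets every place that times the instrument beside every place that analyses it.

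**Step 1. Where it is collected**

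| Place in the protocol | Screening / Visit 0 | Visit 1 | Visit 10 (Day 35) | Visit 11 (Day 63) |
|---|---|---|---|---|
| Summary of Clinical Study Schedule | yes | – | – | – |
| Trial Schedule text | yes | – | – | – |
| Flowchart | yes | – | – | – |
| Visit 0 procedures | yes | | | |
| Observation and inspection items, table | yes | – | – | yes |
| Secondary outcome section | – | yes | – | – |
| Visit 1, 10 and 11 procedures | | not listed | not listed | not listed |
| End of study and Tracking lists | | | not listed | not listed |

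The Visit 11 mark and the Visit 1 statement therefore have no matching procedure in the visit-by-visit text. By contrast, the Coldness Diagnostic Questionnaire is placed at Visits 1, 10 and 11 in both tables and in the outcome section.

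**Step 2. What each version yields per participant**

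- Screening only: 1 value before treatment, 0 after. Change is undefined.
- Visit 1 only: 1 value before treatment, 0 after. Change is undefined.
- Screening and Visit 11: 1 value before treatment and 1 at Day 63. A screening-to-Day 63 change can be formed in all three arms.

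With 3 × 24 = 72 participants, the first two versions give a post-treatment value in 0 of 72. In the third, the later value falls 63 − 35 = 28 days after the nominal week-5 visit. No version has a Day 35 value.

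**Step 3. What each planned analysis needs**

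| Analysis | Measurements needed | Possible under screening-only or Visit 1? | Possible under screening plus Visit 11? |
|---|---|---|---|
| VAS change by pattern indicator (ANOVA, post hoc tests) | 1 | yes | yes |
| Factor analysis, Cronbach's alpha | 1 | yes | yes |
| Items pre/post treatment | 2 | no | to Day 63 only |
| Change compared between three arms | 2 | no | to Day 63 only |

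**Step 4. Which end point the general rule implies.** The overview's Methods row and the Trial Schedule place the end of study at 5 weeks, with the Visit 11 assessment 4 weeks later as follow-up. A change from baseline to the end of trial therefore ends at Visit 10, where this instrument is never taken.

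**Step 5. Whether LOCF fills the gap.** With one value x₀ per participant, carrying it forward gives a change of x₀ − x₀ = 0 for everyone in every arm. That is an artefact and carries no information.

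**The case against.** The strongest reply is that the questionnaire is a baseline classifier. The secondary outcome section relates VAS change to pattern indicators, and the ANOVA takes VAS change as the dependent variable. Both need one pattern measurement. This stands for those analyses, and one of the two remedies adopts it. It does not remove the pre/post and between-arm wording in the overview, the Secondary purpose and the statistical methods.

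A second reply is that the Observation and inspection table does give a before and an after value in all three arms, and that the pattern analysis names no week. This also stands in part: a screening-to-Day 63 change is computable if sites follow that table. A reader might infer that the change analyses fail under every version, and the documents do not support that. What fails under this version is the baseline-to-end-of-trial change, and the Day 63 collection has no support in the Visit 11 procedures.

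Two further strong readings are tempting.

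- A reader might infer that a Day 63 pattern value would be misaligned with the week-5 VAS change it is to explain. The documents do not plan that: no section relates a post-treatment pattern value, or a change in pattern, to VAS change.
- A reader might infer that this secondary outcome yields nothing if collected once. That too is unsupported, because the single-measurement analyses in the working survive.

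The gap between Visit 0 and Visit 1 matters little by itself. It leaves the baseline visit unclear but does not decide whether a post-treatment value exists.

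**Conclusion.** Wrong as written: the schedules contradict one another, and the planned change analyses do not fit them. If sites follow the screening-only sections or the Visit 1 statement, 0 of 72 participants have a post-treatment value and the change analyses cannot be done. If they follow the Observation and inspection table, only a follow-up change to Day 63 is available.

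The damage is limited to the pre/post item analysis and the between-arm comparison of change in this one instrument. The conclusion assumes that the end of the trial in the general principles means the 5-week assessment, as the protocol uses the term elsewhere. If it were taken to mean Visit 11, the table version would supply the change, but the contradiction with the other sections would remain.

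**What to change.** Choose one role for the questionnaire and make every section match it.

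- **Baseline classifier (wording only).** Delete its change analyses from the Statistical analysis row of the overview, the Secondary purpose and the section on analysing validity variables. Remove the Visit 11 mark from the Observation and inspection table. State one and the same baseline visit in both schedule tables, the Trial Schedule text, the flowchart, the Visit 0 procedures and the secondary outcome section. The cost is an edit. What is given up is any statement about change in pattern.
- **Outcome with change.** Keep the change analyses and schedule the questionnaire at Visit 10 in all three arms, in both tables, the flowchart, the Visit 10 procedures and the secondary outcome section. State one baseline visit throughout. Say whether the Visit 11 assessment is kept and, if so, add it to the Visit 11 procedures. The cost is one extra assessment per participant at a visit all arms already attend. It is completed by an evaluator and not by the participant, so it takes rater time, and the protocol's commitment to assessors who are blinded and separate from the treating physician would apply to it.
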